**Methods:**

The project includes an observational study with a before and after design. Implementation of the TERMA model consists of an 8-seminar staff training program. Data sources include questionnaires, medical records, and registries. Quantitative data will be analyzed using descriptive and comparative statistics. To analyze changes between measurements, dependent sample 2-tailed *t* tests will be used for normally distributed data, and the Wilcoxon signed-rank test will be applied when normality is not met. The project will also include qualitative interview studies, which are planned to be analyzed using qualitative inductive content analysis.

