### Quantitative Sources and Collection of Data

Data will be collected from questionnaires, medical records, and administrative registers. Questionnaire data will be obtained from both patients and staff at baseline and 6- and 12-month follow-up. To assess perceived safety, data will be gathered from both patients and staff members using the E13 [15]. The E13 assesses self-reported safety, feelings of security, and violence preventative culture within the hospital wards. Respondents will be presented with 13 statements, and their level of agreement will be rated on a 4-point Likert scale, ranging from (1) “completely disagree” to (4) “completely agree,” with an additional “do not know” option available [15]. The questionnaire assigns a value of “1” to response options 3 and 4 for all items, except for the 3 negative items (items 4, 8, and 12), where a value of “1” is assigned to options 1 or 2 [15]. All other responses are scored as “0.” Thus, the sum score range for each questionnaire was 0‐13 [15].

The OVQ will be used to investigate the organizational culture in the wards. The survey will only be distributed to staff. The OVQ is based on the concepts of the competing value framework, which measures the 4 dimensions within each business: collaboration, creation, competition, and control [20]. These values compete in a very real sense for a business’s limited resources (funding, time, and people). The questionnaire contains 52 items, each rated on a 10-point Likert scale from “disagree” to “strongly agree” [20]. Data regarding incidents of threats and violence, patient and occupational injuries, and the application of coercive measures will be extracted from medical records and the local clinical registry known as MedControl PRO. These data points will be collected in 3 distinct phases: before the introduction of TERMA, at the 6-month juncture following implementation, and upon the culmination of a 12-month period. For staff members, supplementary descriptive data will be collected through a dedicated questionnaire, while background information pertaining to patients will be retrieved from their medical records.

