### Outcomes

The primary outcome will be change in perceived safety reported by both patients and staff, as measured by the E13 scale total score (0‐13), between baseline and 6- and 12-month follow-up assessments. Secondary outcomes include changes in organizational culture, as measured by the OVQ and its subscales between baseline and 6- and 12-month follow-up assessments. Correlation between E13 and OVQ scores at baseline, 6-month follow-up, and 12-month follow-up will be analyzed. The number and severity of aggression incidents from 1 year before baseline to 1 year after conclusion of the study will be analyzed.

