### Statistical Analysis

Descriptive statistics and comparative statistics will be used in the analysis. All data will be analyzed at a group level and reported using means and SDs. To analyze changes between the measurements, the plan is to use dependent sample 2-tailed *t* tests (if data are normally distributed) or the Wilcoxon signed-rank test (if data are not normally distributed). Regression models will be used to explore the relationship between organizational culture and the outcome of the implementation of TERMA. *P* values will be considered statistically significant if they are <.05.

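### A normality check chooses the test for the primary E13 change while every result is a mean and SD, and the named paired tests make no use of incomplete responders' scores

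*Protocol article*

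**What the plan says.** The Outcomes section defines the endpoint: "The primary outcome will be change in perceived safety reported by both patients and staff, as measured by the E13 scale total score", between baseline and the 6- and 12-month assessments. Under Quantitative Sources and Collection of Data, "Questionnaire data will be obtained from both patients and staff at baseline and 6- and 12-month follow-up", and the score is a count of 13 items coded 0 or 1: "Thus, the sum score range for each questionnaire was 0‐13".

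The Statistical Analysis section names one procedure for change. In the first case "the plan is to use dependent sample 2-tailed *t* tests (if data are normally distributed". The alternative, for every other case, is worded there as "or the Wilcoxon signed-rank test (if data are not normally distributed". The Abstract repeats the rule: "the Wilcoxon signed-rank test will be applied when normality is not met". Whichever test is used, "All data will be analyzed at a group level and reported using means and SDs". The significance rule is that P "values will be considered statistically significant if they are <.05". Regression is named only for the link between organizational culture and the outcome of implementation. The article does not say how normality is judged, or whether it is judged on the scores or on the paired differences.

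**The concern.** Two features of the named method matter for the primary result.

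1. **Test and reported quantity can part.** The signed-rank test asks whether the paired differences are symmetric about zero. It tests the mean change only if they are symmetric. If the check selects it and the changes are skewed, the P value answers a different question from the mean printed beside it. Because the check depends on the data and on sample size, patients and staff, or 6 and 12 months, may also be tested differently.
2. **Incomplete responders add nothing.** A paired test needs a baseline and a follow-up value from the same person. The 6- and 12-month comparisons can then rest on different people, and a 6-month score is not used at 12 months if the 12-month score is missing. If staying depends on the scores, the mean change in complete pairs is not the mean change in those enrolled.

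**Working it through.** The article states no sample size, SD, effect size or dropout rate, so there is no planned figure to reproduce. From the documents come the 0–13 integer score, the three waves, the two tests, the 0.05 level, about 290 staff, and 84 rehabilitation rooms (some shared) as a rough guide to patient numbers before eligibility and consent. All other inputs below are assumptions.

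**Step 1: which test is chosen.** Assume the check is a Shapiro-Wilk test at 0.05 (the article names none). Simulate symmetric integer changes with true mean 0, 3,000 runs per sample size.

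| Pairs | Normality rejected | Error rate of the two-stage rule |
|---|---|---|
| 40 | 24% | 4.9% |
| 60 | 38% | 5.4% |
| 100 | 75% | 4.4% |
| 150 | 99% | 5.0% |

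Sample size alone can decide the test, but with symmetric changes the error rate stays near 5%.

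**Step 2: skewed changes with true mean 0.**
- Mild skew: 75% of people change by +1 and 25% by −3, plus noise of −1, 0 or +1. Mean = 0.75×1 − 0.25×3 = 0.
- Strong skew: everyone gains 0, 1 or 2 with probability 0.35, 0.40 and 0.25, and 15% also fall by 6. Mean = 0.40 + 0.50 − 0.15×6 = 0; median +1.

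In both cases the rule selects Wilcoxon in every run.

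| Case | Wilcoxon rejects | Paired t rejects |
|---|---|---|
| Mild skew, 40 to 200 pairs | 5.7% to 8.4% | 4.8% to 5.8% |
| Strong skew, 40 / 60 / 100 / 150 pairs | 26.5% / 34.5% / 43.6% / 59.8% | 7.0% / 6.2% / 5.0% / 5.6% |

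The strong case is a deliberate extreme. It shows that a small P value can stand beside a mean change near zero.

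**Step 3: complete pairs when leaving depends on observed scores.** Assume 150 enrolled, SD 3, correlation 0.6 between any two waves, about 63% retained at 12 months, and no true change. SD of change = 3×√(2×(1−0.6)) = 2.68. Standard error with 0.63×150 ≈ 94 pairs = 2.68/√94 ≈ 0.28.

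| Odds ratio of staying per SD | Complete-pair bias (size) | Likelihood estimate, all waves |
|---|---|---|
| 1.2 | about 0.1 | about 0 |
| 1.5 | about 0.2 | about 0 |
| 2.7 | about 0.4 | about 0 |

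The bias is positive if people whose score fell by 6 months leave more often (+0.38 to +0.43 at odds ratio 2.7, depending on whether the SD is that of the score or of the change). It is negative if people with a low baseline leave more often (−0.37 to −0.38). Standard errors of the two estimates are about equal (0.28 and 0.27), so the largest bias is about 0.4/0.28 = 1.4 standard errors.

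To see what this requires: if the overall mean change is 0, a share d leaves, and stayers' mean change exceeds leavers' by g, then stayers' mean change = d×g. With d = 0.37, a bias of 0.4 needs g = 0.4/0.37 ≈ 1.1 points, and a bias of 0.1 needs g ≈ 0.3 points.

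**Step 4: leaving depends on a stable personal trait.** Keep the same set-up, but let staying depend on the person's underlying level and not on the observed scores. The trait cancels in the within-person difference, so complete pairs give 0.00. The likelihood estimate predicts leavers from stayers with the same observed scores and is off by +0.08 at a slope of 0.4 per SD and +0.21 at 1.0. Across the slopes tried, the range is about 0.05 to 0.2 points.

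**The case against.** **Missing data.** The article does not say that incomplete responders are dropped; it names paired tests and is silent on missing values. A full protocol or analysis plan that is not shown could add imputation before a paired test. This stands. A reader might infer that leavers are certain to be discarded and the result biased, and the document does not support that. The point rests on the method that is named and not on a missing section. Patients are in compulsory care with a median duration of 7.5 years (Introduction), so their turnover within 12 months may be small. That leaving is related to feeling unsafe is conjecture.

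**The remedy's assumption.** A reader might infer that the mixed model needs a weaker assumption. It does not: Step 4 gives a case in which complete pairs are unbiased and the model is not.

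**The switch.** A reader might also infer that choosing the test after a normality check inflates the error rate in general. Step 1 shows that it does not when changes are symmetric, and mild skew adds little. Printing a mean and SD beside a Wilcoxon P value is common practice. Patients and staff are separate populations with no planned comparison between them, so using different tests would invalidate neither result. What remains is that the criterion for the switch is undefined and that under skew the P value and the reported mean answer different questions.

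**Conclusion.** The point holds in a moderate form. The test switch and the uniform reporting of means and SDs are explicit. The use of complete pairs follows from the tests as named. The cost of the switch ranges from negligible with symmetric changes to serious only under strong skew. The cost of ignoring incomplete responders is unknown, because the article gives neither a dropout rate nor a mechanism. On the assumptions in Step 3 it is about 0.1 to 0.4 points on the 0–13 scale, of either sign, and it is 0 under the mechanism in Step 4. The analysis should be changed, because a better-defined one is available from data already planned. This does not show that the trial's result will be wrong.

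**What to change.** Prespecify one analysis of mean change, run separately for patients and staff: a linear mixed model on all E13 scores at baseline, 6 and 12 months, with time as a factor and everyone with at least one score included. Report the mean changes with 95% CIs, using robust or bootstrap standard errors because the score is bounded. Drop the normality check. Keep the complete-pair paired t and Wilcoxon tests as a sensitivity analysis. Report retention at each wave and the baseline E13 of completers and leavers.

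The cost is analysis wording only; no new data are needed. The drawback is reliance on missing at random, which leaves a bias of about 0.05 to 0.2 points in the stable-trait case. The model and complete-pair results should therefore be shown side by side, and a clear difference between them discussed. The Results section expects the quantitative analysis to be finished by early 2026, so the change should be recorded and dated before the outcome data are examined. If they have already been examined, it should be labelled as made afterwards.

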### Qualitative Data Collection and Analysis

This project will also include qualitative design using semistructured individual interviews with both patients and staff members. Approximately 15 to 25 interviews are estimated to be suitable for answering the research questions in each study. The plan is to analyze data collected from the interview with qualitative inductive content analysis, but the decision if the method is appropriate will be based on the depth of the collected data and research questions [32-35]. Incorporating a qualitative design will facilitate greater understanding of patients’ perceptions of threatening and violent incidents, their experiences with coercive measures, and the use of TERMA within a forensic psychiatric inpatient environment. It will also offer valuable insight into staff perspectives regarding their approach to working with TERMA, their reactions to instances of threat and violence, and the resulting impact of these dynamics on the overall work environment within a forensic psychiatric inpatient setting.

### Patient and Public Involvement

To our knowledge, there was no patient and public involvement in the development or design of the TERMA model. In this research project, we sought to address this by actively involving patient representatives in various stages of this study. They were consulted about data collection and gave input on the choice of outcome measures to ensure that they are relevant from a patient perspective. In addition, we plan to engage them in the interpretation of the data. For the qualitative studies, the patient representatives will be engaged in the design of the interview guides as well as the interpretation of data. Finally, the patient representatives will be involved in the dissemination of the findings for all the studies.

### Ethical Considerations

The study has been approved by the Swedish Ethical Review Authority (2023-02451-01). All steps of the project have been designed to adhere to the principles outlined in the Declaration of Helsinki [36]. Written and verbal informed consent will be obtained from all participants, with clear information provided about their right to withdraw from the study at any time. The vulnerable nature of patients in forensic psychiatric care has been taken into consideration during the planning of the project, and special consideration will be taken when asking patients to participate in the project. They will also be reassured that participating in this research study will have no impact on their usual care. Permission obtained from the treating physician at each ward will be included in the project. Participants received no compensation to be part of the study. The methods used will be carefully considered to align with the study’s purpose, and the principles of confidentiality and integrity will be strictly maintained throughout the process. The collected data will be stored in a secure database maintained by the department and the university. This database is anonymized, and all analyses will be conducted on deidentified data, minimizing the risk of breaching confidentiality. The collected data are treated confidentially and presented in a way that ensures participants cannot be identified.

## Results 

Recruitment of participants began in July 2023 and concluded by the end of 2024. Collection of data from patient and staff questionnaires will be completed 13 months thereafter. Data from administrative registries will be collected retrospectively for the entire period. Data collection and analysis of quantitative data are expected to be completed by early 2026. Collection of data for the qualitative studies is planned for the second half of 2025 and 2026, and analysis is planned for 2026 and 2027. Results from this project will be published in peer-reviewed scientific journals and presented at international conferences.

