## Methods

### Overview

This study uses an observational before and after design. The choice of TERMA was a pragmatic one, as it was being implemented in the clinic. However, the research design, including research questions, outcome measures, and methods of analysis, was not influenced by the clinic. The project was registered on ClinicalTrials.gov (NCT05932108) before starting the study. The protocol complies with the Standard Protocol Items: Recommendations for Interventional Trials (SPIRIT) [30,31], and the results will be reported according to established recommendations.

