### Enrollment

All patients in the included wards will be assessed for eligibility by a member of the research team together with the ward staff and the responsible physician. Eligible patients will be given information about the study and asked to participate. Patients will be informed, both orally and in writing, that participation in the study is voluntary. They will also be assured that they can withdraw their consent at any time, and their decision to participate or not will not affect their care. Patients who indicate their willingness to participate will be issued a consent form. When returning the completed consent form, patients will receive the E13 questionnaire, which will include a randomly assigned identification number to ensure confidentiality throughout the research process.

All staff will be assessed for eligibility by a member of the research team. Eligible staff will receive detailed information about the study and be invited to participate. Information will be provided both orally and in writing. Staff who express their willingness to participate will be provided with a consent form. Upon returning the completed consent form, staff will receive 2 questionnaires (the E13 and the Organization Values Questionnaire [OVQ]), each coded with a randomly assigned identification number to ensure confidentiality throughout the research process.

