These levels are designed to correspond with specific situational demands and environmental factors, optimizing their relevance and applicability. The *primary level* centers on the patient’s daily behavior and overall health status. It involves proactive measures aimed at understanding the patient’s emotional state, as well as managing stress and anxiety. Building trust and establishing balanced roles are key components at this stage. At the *secondary level*, the focus shifts to risk assessment and violence management. The aim is to cultivate mutual understanding between the patient and health care workers regarding the situation. The emphasis is on finding common ground and agreeing on acceptable solutions while preparing for further escalation if necessary.

When violence becomes inevitable, the *tertiary level* is activated. Here, the primary goal is to create a calm and secure environment for the patient, other patients, and staff. Clear leadership and low-intensity approaches are vital for diffusing tension, and physical restraint, if required, is executed with precision. Following the resolution of the situation, a situational analysis is offered to the patient to enhance understanding and prevent future incidents.

The implementation of TERMA is conducted through a staff training program consisting of 8 seminars. The seminars are divided into 4 theoretical sessions and 4 practical training sessions. The staff members first receive theoretical knowledge, followed by hands-on practice in restraint and self-defense techniques. This mixed format facilitates a holistic understanding of TERMA and equips staff with the skills necessary for implementation. The TERMA intervention will be uniformly implemented across all wards of forensic psychiatry at the Sahlgrenska University Hospital.

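### Baseline is taken at consent over up to about 18 months with no link to the TERMA start, so the paired before-after contrast is not secured

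*Protocol article*

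**What the plan says.** All references are to the protocol article.

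- **Baseline.** Under Enrollment, for patients: "When returning the completed consent form, patients will receive the E13 questionnaire". For staff: "Upon returning the completed consent form, staff will receive 2 questionnaires". The first measurement therefore follows each person's own consent.
- **Recruitment period.** Under Results: "Recruitment of participants began in July 2023 and concluded by the end of 2024". The next sentence reads "Collection of data from patient and staff questionnaires will be completed 13 months thereafter".
- **Follow-up.** Under Quantitative Sources and Collection of Data: "Questionnaire data will be obtained from both patients and staff at baseline and 6- and 12-month follow-up". The event from which 6 and 12 months are counted is not stated.
- **Register and medical-record data.** The same section ties these to the intervention: "before the introduction of TERMA, at the 6-month juncture following implementation", and then the end of a 12-month period. The Outcomes section counts incidents from one year before baseline, without saying which baseline is meant.
- **Primary contrast.** Outcomes defines it as the change in E13 total score from baseline to 6 and 12 months. Statistical Analysis tests it with a paired t test or the Wilcoxon signed-rank test.
- **Roll-out.** Design and Implementation of the TERMA Model says "The TERMA intervention will be uniformly implemented across all wards", by means of eight staff seminars. No start date or ward order is given.

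**The concern.** A before-after study without a concurrent control rests on one condition: the first measurement precedes the intervention and the second follows it. Here the first measurement is triggered by consent, and consents were collected over a period that may be longer than the longest follow-up. No stated rule requires a baseline to precede TERMA on the respondent's ward, or a follow-up to come after it. The paired test as described pools every pair, whichever side of the start its two forms fall on.

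The E13 change could then be a mixture of before-before, before-after and after-after differences. Such a mixture does not estimate the change associated with introducing TERMA. A null result could reflect dilution, and a positive one could include background drift. The reader could not tell which.

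**Working it through.** The article gives no figure of its own to reproduce, so the check is calendar arithmetic.

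**Inputs**
- Recruitment window W: July 2023 to the end of 2024 (Results). From 1 July 2023 to 31 December 2024 is 18.04 months; from 31 July 2023 to 31 December 2024 is 17.05. I use W = 17 and W = 18. These are upper values, because recruitment ended *by* the end of 2024.
- Follow-up f: 6 and 12 months (Quantitative Sources and Collection of Data).
- Baseline at consent (Enrollment).
- TERMA start t, in months from the opening of recruitment: not given, so varied.

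**Reading A: one clinic-wide start, follow-up counted from consent, consents uniform over W (all three are assumptions)**

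For a person consenting at month c:
- the baseline is post-TERMA if c > t, share (W − t)/W for t between 0 and W;
- the follow-up is pre-TERMA if c + f < t, share max(0, (t − f)/W).

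The two cases exclude each other, so the share of pairs that do not bracket the start is their sum. For t between f and W the sum is (W − t + t − f)/W = (W − f)/W, which does not depend on t. Any t outside that range gives a larger share, so this is the minimum.

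- 12 months: (18 − 12)/18 = 33%; (17 − 12)/17 = 29%.
- 6 months: (18 − 6)/18 = 67%; (17 − 6)/17 = 65%.

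For W = 18:

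| Start t (months) | Baselines post-TERMA | 12-month forms pre-TERMA | 12-month pairs not bracketing | 6-month forms pre-TERMA | 6-month pairs not bracketing |
|---|---|---|---|---|---|
| 0 | 100% | 0% | 100% | 0% | 100% |
| 6 | 67% | 0% | 67% | 0% | 67% |
| 12 | 33% | 0% | 33% | 33% | 67% |
| 15 | 17% | 17% | 33% | 50% | 67% |
| 18 | 0% | 33% | 33% | 67% | 67% |

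Under this reading no start date lets all pairs bracket TERMA, because W exceeds f.

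**Reading B: one start at the end of recruitment, follow-up counted from that start**

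Take a start in about January 2025. All baselines are then before TERMA and all follow-ups after it, so the non-bracketing share is 0%. The 12-month form falls in January 2026, inside the stated limit of 13 months after recruitment closed (end of January 2026). The interval from baseline to the 12-month form is 12 months for the last person enrolled and 18 + 12 = 30 months for the first.

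**Reading C: wards start one after another, with baselines taken before each ward's start**

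The problem does not arise. The article does not describe such a scheme.

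**Can the text decide between the readings?** The 13-month limit fits Reading A (last consent + 12 months + 1 month) and Reading B equally well, so it does not settle the anchor.

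**The case against.** The strongest reply is that the article demonstrates no contamination. Reading A needs two premises that it does not state. "The TERMA intervention will be uniformly implemented across all wards" can mean the same programme everywhere, not the same date, and eight seminars for about 290 staff do not suggest an overnight switch. Nor does the article say that the 6- and 12-month forms run from consent. Roll-out schedules and visit windows are also details that an article commonly leaves to the full protocol. All of this stands, and it makes the percentages conditional.

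It does not remove the point. The difficulty is more than an absent date: the contrast that *is* specified pairs a consent-triggered baseline with later forms and pools all pairs, while the register phases in the same article are anchored to TERMA.

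A reader might be tempted to infer four stronger things, none of which the documents support:

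- *That some baselines must be post-TERMA or some follow-ups pre-TERMA.* Readings B and C both avoid this.
- *That training had begun before baselines were taken*, from "The choice of TERMA was a pragmatic one, as it was being implemented in the clinic". That sentence explains why this model was chosen. Elsewhere the roll-out is described in the future tense, and data from before the introduction are planned.
- *That the register data cannot be aligned with the questionnaires.* Results says they are collected retrospectively for the whole period, so they can be cut at any time zero.
- *That the bias is necessarily toward no change.* Dilution follows only with a step effect and no background trend. In an uncontrolled design, pairs that do not bracket the start may carry drift in either direction.

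**Conclusion.** The point holds in a conditional form. As written, the plan does not secure that each primary E13 pair compares before with after TERMA.

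- With one clinic-wide start, consent-anchored follow-up and uniform enrolment over 17 to 18 months, at least 29-33% of 12-month pairs and 65-67% of 6-month pairs cannot bracket the start. A shorter actual recruitment window would lower these figures.
- With follow-up anchored to one start at the end of recruitment, all pairs bracket it. The paired test then pools intervals of about 12 to 30 months under a single 12-month label, which leaves it open to secular change.
- With staggered starts and baselines taken before each one, the problem is avoided, but the article would have to say so.

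Under the first two readings the primary result is hard to interpret without a stated time zero. Under the third, a sentence of clarification would be enough. The direction of any bias is not established. Since recruitment is closed, the remedy lies in the analysis, and it should be fixed before the data are analysed.

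**What to change.** 1. State the TERMA start, by ward if staggered, and the event from which questionnaire follow-up is counted.
2. Define time zero as the first TERMA seminar on the respondent's ward.
3. Classify each questionnaire as pre-TERMA or by months since ward start, using recorded completion dates, or consent and distribution dates if those are what is held. The article does not say which dates or ward identifiers were kept, so this must be checked first.
4. Restrict the primary before-after contrast to respondents with a pre-start baseline and a follow-up in a pre-specified window around 6 or 12 months after ward start. Report how many pairs qualify and the distribution of the baseline-to-follow-up interval.
5. Analyse the remaining questionnaires in a secondary model with actual time since ward start. If starts were staggered, add calendar time, so that wards not yet started inform the background trend.
6. Cut the register and medical-record data at the same time zero, and say which baseline the incident period in Outcomes refers to.

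The cost is a change of analysis wording, a list of ward start dates from the training schedule, and fewer respondents in the primary paired set. No new data from participants are needed if usable dates were kept. If they were not, the limitation should be stated and the change should not be attributed to TERMA.
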